## 1. Background and Purpose

Thrombolysis with intravenous tissue Plasminogen Activator (tPA) when given to carefully selected patients within 4.5 hours of the onset of symptoms of acute ischaemic stroke reduces the risk of dependency.^2,5^ It is estimated that at least 10% of stroke patients may be eligible for thrombolysis and NICE has a target implementation that within 5 years 10% of ischaemic stroke patients < 80 yrs should be treated with tPA.^5^ Currently less than 0.7% of patients with acute ischaemic stroke in the UK receive this treatment (although for individual centres in the UK 5-10% of acute ischaemic stroke patients admitted to their service receive this treatment).^4,8^ There are two factors that contribute to this poor access to acute stroke treatment: an inadequate emergency care response; and insufficient public awareness of the signs and symptoms of stroke or the need to treat it as a medical emergency.

Low thrombolysis rates are in part due to delays in seeking medical attention following the onset of symptoms. In 2002 the median time between onset of symptoms and arrival to hospital in the UK was 6 hours with only 37% arriving within 3 hours.^1^ Early recognition and rapid response to the symptoms of stroke by patients and bystanders are important dimensions of improving outcome following stroke.^3^

In a recent systematic review^6^ we found that, while patients and the general public in the UK regarded stroke as a serious condition which required emergency treatment, they had limited knowledge of the symptoms of stroke. In addition, although members of the general public reported that they would call an ambulance in the event of a stroke, in practice both patients and witnesses often initially contacted a general practitioner, which had a major impact upon time from symptoms to admission. A significant number of patients and witnesses waited to see if symptoms resolved. Thus although people report they consider stroke to be an emergency condition, observed behaviour suggests this knowledge does not result in an appropriate response.

A key component of the English National Stroke Strategy is to ensure that patients with acute stroke are treated as a medical emergency.^3^ The strategy seeks to ensure that ‘members of the public and health and care staff are able to recognise and identify the main symptoms of stroke and know it needs to be treated as a medical emergency’. Over the next 3 years £12 million will be invested in a multi-faceted strategy to improve awareness of, and response to, stroke.

One of the objectives of the broader NIHR-funded DASH (Developing and Assessing Services for Hyperacute stroke) programme of research being undertaken by our research team, is to provide evidence to support this work by seeking to understand why patients and those who witness a stroke in the UK do or do not seek emergency help following a stroke. As part of that programme, this study will investigate how and why emergency medical services are accessed at the onset of (acute) stroke by people with stroke and ‘witnesses’ to the stroke e.g. family members/friends/carers/bystanders who were present at the time of stroke or who found the patient with stroke and made initial contact with medical services. We define ‘access to emergency services’ as deciding whether, or not, to immediately call emergency medical services. The results of this work will inform the development of interventions to increase awareness of stroke symptoms and the accessing of stroke services at the onset of stroke among stroke patients and the general public.

## 2. Aim of DASH 1 Qualitative Study

To understand the reasons individuals contact or delay contacting emergency medical services in response to symptoms of stroke in order to support the development of an intervention for raising patient and public awareness of stroke symptoms; thus increasing rapid access to hyper-acute stroke services for people with acute stroke.

## 3. Aim of this work

To identify, describe and understand how and why patients and witnesses did, or did not, seek immediate emergency medical assistance following the onset of stroke symptoms.

## 4. Timescale

The qualitative work with stroke patients and witness(es) will take 16 months from the 1^st^ November 2008. This consists of two months to obtain ethical and R&D approvals, six months to recruit and interview patients and witnesses, and eight months for analysis and writing up.

## 5. Study Methods

We will conduct a qualitative study of reported actions in accessing, or not accessing, emergency medical services by stroke patients and ‘witness(es)’ at the onset of stroke symptoms. This will be undertaken through the use of semi-structured interviews of stroke patients and witness(es).

The topic guides for the interviews will be developed in collaboration with people with stroke, identified through the North East Stroke Research Network.

A situational analysis^7^ will be used in the analysis of interview transcripts. Situational analysis builds on traditional grounded theory and involves constructing the situation of inquiry empirically through mapping. Situational maps lay out the major human, non-human, discursive and material elements in the research situation of concern and provoke analysis of relations among them, thus allowing the deeper exploration of themes which are raised by participants or are implicit in the interview transcripts.

## 6. Study Design Overview

We will undertake face-to-face interviews with:

- Patients within two weeks of stroke;
- ‘witness(es)’ who were instrumental at the time of the stroke in accessing, or not accessing, emergency services.

## 7. Setting

Stroke units in NHS North of Tyne; Newcastle upon Tyne Hospitals NHS Foundation Trust and Northumbria Healthcare NHS Foundation Trust.

## 8. Sample

Up to 48 participants (24 patients and 24 ‘witnesses’) who made the initial call to NHS services which led to the patient being admitted to hospital following a stroke event. The sample will comprise the individuals who had a stroke, and ‘witnesses’ (those who were present at the time of stroke/found the patient and made the initial telephone call), giving a total of 48 separate events.

The sample of 48 will consist of 4 categories of participants (the caller, either patient or witness, for an individual with a stroke event) who:

- was admitted to hospital **via emergency care** (999 or direct to A&E) **within one hour** of the onset of stroke
- was admitted to hospital **via emergency care** (999 or direct to A&E) **after one hour** following the onset of stroke.
- was admitted to hospital **via GP or other routes within one hour** following the onset of stroke ,
- was admitted to hospital **via GP or other routes after one hour** following the onset of stroke .

Those who had a stroke during their sleep where the time of onset of symptoms is not known **will not be excluded**, but will be included to ascertain what action they took on becoming aware of the stroke event, i.e. upon wakening.

As patients who are too ill will be excluded from participating, it is likely that our patient sample who made the call themselves will include more patients with less severe stroke events, However, it is less likely that patients with severe stroke will have made calls and more likely that they will have been made on their behalf by informants who will be our witness sample. Thus the overall sample will include both severe and less severe events.

**Participant sample matrix**

|  | Service accessed via 999 or direct to A&E | Service accessed by other route (e.g. GP & NHSDirect) |
| --- | --- | --- |
| Patients admitted within 1 hour of stroke onset | 12 | 12 |
| Patients admitted after 1 hour of stroke onset | 12 | 12 |

As this is a qualitative study the sample size is not designed to provide statistically representative samples, but will be large enough to capture the range of experience and actions for each section of the sample matrix. If this is felt not to have occurred we will sample until there is no new data.

## 9. Identification and Recruitment

Research collaborators in each of the three stroke units will assist in recruitment and assessment of those eligible to participate in the study. The stroke units in this study are involved in other aspects of the broader DASH programme of research.

Up to 48 patients and witnesses, representing 48 different events, will be recruited across three sites.

*Patient recruitment*

Potential patient participants will be identified by clinical staff on admission to the stroke unit and approached by Stroke Research Network (SRN) research nurses on the stroke unit 1-2 days post-stroke. The SRN research nurse, who will have been briefed on the research study, will ask patients if they were the person who made the call leading to hospital admission and if so whether they are willing to participate in the study. SRN research nurses will provide patients with information (written and verbal) to allow the patient to make an informed decision about participation. The research team will be notified when a patient has agreed to take part in the study and a meeting will be arranged with the researcher to provide further information and/or an interview (as per the patient’s wishes). Interviews will take place on the stroke unit for in-patients. Those who have been discharged early will be given the choice of being interviewed either in their own home, on the stroke unit or at the university. Prior to the interview commencing, written consent will be sought from the patient. (see Appendix C). Patients will be interviewed at 7 +/- 2 days post-stroke.

Patients will only be interviewed if they are deemed to have capacity adequate for engagement in decision-making at the time of enrolment and if they also have capacity for interview at the time of consent. Capacity will be determined by a member of the clinical team who is responsible for the care of the patient. All patients with diagnosis of acute stroke will be eligible, irrespective of treatment received.

*Witness Recruitment*

When a patient is approached by the SRN research nurse and asked if they were the person who made the call leading to hospital access, if they say that a witness made the call, then that witness will be approached to ascertain if they would be willing to be contacted about participation in the study. They will be given a copy of the witness information sheet (appendix B). If they indicate that they are willing to participate, the research associate will make contact and provide any further information required/answer any questions and arrange a time and place for the interview. We will also recruit witnesses by direct contact through SRN research nurses with accompanying carers/relatives to ensure we collect data from people involved in making contact with NHS services after severe stroke events. We will follow the procedures for recruitment as for patients, with a separate written consent form for witnesses (Appendix D). Witnesses will be given the choice of being interviewed in their own home, at the hospital or at Newcastle University.

Patients and witnesses will be interviewed independently. It is anticipated that a patient may request that a carer/significant other person is present with them during the interview, but as the categories ‘patient’ and ‘witness’ are mutually exclusive this should not impact negatively on the study

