## 11. Data Collection

*Detailed steps:*

Potential interviewees will be identified at admission or during clinical contact within 1-2 days post-stroke by SRN research nurses. The responsible clinician will assess patient capacity for involvement in the research according to the Mental Capacity Act 2005.

If patients are deemed to have capacity, SRN research nurses will ask them if they were the person who made the call leading to hospital access. If so the SRN nurses will tell the patient about the study and provide potential participants with a copy of the patient information sheet (appendix A). If the patient was not the person who made the call leading to hospital access they will be asked who did. If the patient is not capable of providing this information the SRN research nurse will ask those family and friends present to identify the individual and will provide potential participants with a copy of the witness information sheet (appendix B).

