After a period for reflection (24-48 hours), the SRN research nurse will approach potential patient participants to ascertain willingness for involvement. The SRN research nurse will alert the DASH research team in order that they may visit the ward and be introduced to the potential participant. Potential participants may also contact researchers directly as per information sheet details if desired. The Research Associate will be introduced to patients by a clinical member of staff and make first face to face contact with potential interviewees during days 3-5. At this point the research associate will confirm the potential interviewee has received and understood the information sheet detailing the study, answer any questions and seek their willingness to proceed. If willing, an interview time and place will be arranged. If not obtained at first contact, written consent will be sought at time of interview at 7 +/-2 days post-stroke. The patient may choose to have another person present, therefore interviews may take place with more than one person. ‘Witness’ details will be elicited from the patient (or their families/friends) and they will be given the information sheet by the SRN research nurse. If they assent to be contacted, the research associate will make contact, confirm they have received and understood the information sheet detailing the study, answer any questions and seek their willingness to proceed. Interview and consent procedures will be the same as that for patient participants. Witnesses will be interviewed separately.

Interviews are expected to last between 20 minutes to one hour.

Topic guides will be based on existing evidence and will be developed iteratively in collaboration with patients, stroke researchers and clinicians. Patient and carer representatives from the local Stroke Research Network and DASH groups will be asked to review the topic guide.

Interviews will include questions about:

- their views about what was happening and what they should do about it;
- their actions at the onset of stroke symptoms and why;
- what their concerns and fears were at that time;
- their knowledge of the signs and symptoms of stroke at that time;
- awareness of stroke as a medical emergency at that time;
- their knowledge about available treatment for stroke;
- what advice on signs and symptoms they sought at that time;
- what knowledge of medical services for stroke they had at that time;

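### The 1-2 day patient approach is counted from stroke rather than admission, so followed literally it passes over late arrivals in a study of why people delay

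*Protocol*

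**What the plan says.** **Approach.** Protocol Section 9 has clinical staff identify patients on admission to the stroke unit. They are then approached by "research nurses on the stroke unit 1-2 days post-stroke". Section 11 words the identification step differently: "Potential interviewees will be identified at admission or during clinical contact within 1-2 days post-stroke by SRN research nurses".

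**Reflection and first contact.** Section 11 then allows 24 to 48 hours for reflection, after which the research associate is to "make first face to face contact with potential interviewees during days 3-5". It does not say what those days are counted from.

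**Interview.** Section 9 states: "Patients will be interviewed at 7 +/- 2 days post-stroke". Section 11 agrees, saying that, if not already obtained, "written consent will be sought at time of interview at 7 +/-2 days post-stroke". The design overview in Section 6 gives a looser limit: "Patients within two weeks of stroke".

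**Eligibility.** Section 9 also states: "All patients with diagnosis of acute stroke will be eligible, irrespective of treatment received". The exclusions in Section 10 concern age, capacity, communication and language, not time since onset. The matrix in Section 8 assigns 12 + 12 = 24 of its 48 places to admission after one hour, with no upper bound.

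**The concern.** Section 2 makes the reasons for contacting emergency services, or for delaying contact, the subject of the study. A recruitment clock that starts at onset is itself a function of delay: the longer someone waits, the less of the window is left when they reach the ward. Someone admitted after day 2 was not on the unit when the approach was due.

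The after-one-hour cells could then be filled entirely by people who arrived within about two days. Reasons particular to very long delay could be thin or absent in the transcripts, and so in the awareness intervention that the work is meant to support. The rule in Section 8 to continue sampling until nothing new emerges would not reveal the gap, because themes can appear saturated within the group that the procedure reaches.

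**Working it through.** The protocol gives no figure to reproduce here. The check is interval arithmetic on the stated windows, in days after stroke unless noted.

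**1. The steps as written**

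| Step | Section | Timing | Counted from |
| --- | --- | --- | --- |
| Approach by research nurse | 9 | days 1-2 | stroke |
| Reflection | 11 | 24-48 h = 1-2 days | information given |
| First research-associate contact | 11 | days 3-5 | not stated |
| Interview | 9, 11 | 7 - 2 = day 5 to 7 + 2 = day 9 | stroke |
| Outer limit for patient interviews | 6 | day 14 | stroke |

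**2. Early arrivals.** Approach plus reflection ends between 1 + 1 = day 2 and 2 + 2 = day 4. Contact on days 3-5 and interview on days 5-9 follow. The sequence works.

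**3. Late arrivals.** Let d be the day of admission. An approach on the unit on days 1-2 requires d ≤ 2. For d > 2 the step cannot be carried out as written. The cut-off is about 48 hours, or just under 72 hours if calendar days are counted with the stroke on day 0.

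**4. Room left by the later steps if only the approach were relaxed**
- Using reflection and the day 9 limit alone, the latest workable approach is 9 - 2 = day 7 (48 h reflection) or 9 - 1 = day 8 (24 h).
- If the contact on days 3-5 is also counted from stroke, it is 5 - 2 = day 3 (48 h) or 5 - 1 = day 4 (24 h).

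So the later windows narrow the room for late arrivals. How much depends on the unstated origin of days 3-5.

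**5. Counting approach and contact from admission.** First contact then falls on days d + 3 to d + 5. Section 9 allows the first meeting with the researcher to be the interview.
- Interview by day 9: d + 3 ≤ 9 gives d ≤ 6 at the quickest; d + 5 ≤ 9 gives d ≤ 4 at the slowest.
- Interview by day 14: d + 3 ≤ 14 gives d ≤ 11; d + 5 ≤ 14 gives d ≤ 9.

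Using the limit in Section 6 moves the latest workable admission from day 4-6 to day 9-11.

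**6. Counting the interview from admission as well.** A patient admitted on day 6 would be interviewed between 6 + 5 = day 11 and 6 + 9 = day 15, which can pass the two-week limit.

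**7. Size.** The only delay figures, in Section 1, are a median of 6 hours from onset to arrival and 37% arriving within 3 hours. Neither says anything about arrival after 48 hours.

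**The case against.** The strongest reply is that the 1-2 day figure describes procedure and is not an entry criterion. Eligibility is open, Section 10 excludes nobody for arriving late, and the mention in Section 11 of identification at admission can be read to cover a later admission. A reader might infer that anyone presenting late cannot enter the study. The documents do not support that. What stands against the reply is that nurses recruit by the procedure, and identification at admission does not alter the approach timing in Section 9.

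The point also reaches witnesses less directly. Section 9 adds recruitment by direct contact with accompanying carers and relatives and gives no day limit there. The patient timings apply to witnesses only through cross-references in Sections 9 and 11.

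A reader might also infer that days 5-9 contradict the two-week wording in Section 6. They do not: days 5-9 lie wholly within 14 days, so every interview that meets Section 9 also meets Section 6. An overview may give the outer bound and the detailed sections the working window.

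Finally, an early interview tied to onset limits recall error in a study of what people thought and knew at the time. That is a good reason not to move the whole interview window to admission. It is no reason to count the approach from onset.

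**Conclusion.** The point holds as a defect in the recruitment timetable. Read literally, the approach step leaves out patients admitted more than about two days after onset, which fits neither the open eligibility statement nor the unbounded after-one-hour cells. The days 5-9 interview window tightens this. The selection runs against the longest delayers, the people at the far end of the behaviour under study.

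The size of the loss cannot be stated. It is tempting to fit a curve to the median and the 37% and read off a tail, but two points fix two parameters with nothing left to test the fit, and the result would be extrapolated eightfold, from 6 to 48 hours. Nor is a population share the natural measure for a purposive sample that the protocol says is not meant to be statistically representative. What is at risk is the range of experience captured.

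The conclusion assumes that staff follow the timing as written. If they already approach late arrivals whenever they are admitted, the defect is one of wording only. It is a cheap improvement, not a fault that undermines the study.

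**What to change.** In Sections 9 and 11, count the approach (1-2 days) and the first research-associate contact (days 3-5) from hospital admission, and state that origin for both. Keep 7 +/- 2 days post-stroke as the target interview time, adding that patients who present late may be interviewed up to the two-week limit in Section 6. Record each participant's onset-to-interview interval and consider it when interpreting late presenters' accounts. Strokes during sleep, which Section 8 includes although onset time is unknown, need a stated starting point for that interval.

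The cost is a change of wording and one recorded item. Late presenters will be recalling events from somewhat further back, up to 14 days instead of 9, and the recorded interval makes this visible. Patients admitted after about day 9-11 would still fall outside the two-week limit; the protocol should state this as a limit on what the study can say about very long delay.

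### The sample matrix includes people who went direct to A&E, but the participant definition and screening question recognise only someone who made a call

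*Protocol*

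**What the plan says.** Section 8 and the participant sample matrix divide the sample by time to admission (within or after one hour) and by route. One route is "Service accessed via 999 or direct to A&E"; the other is GP, NHS Direct or similar. Each of the four cells has 12 places.

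The rules on who may fill those places are all written in terms of a call:

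- Section 8, whole sample: people "who made the initial call to NHS services which led to the patient being admitted to hospital following a stroke event".
- Section 8, witnesses: "those who were present at the time of stroke/found the patient and made the initial telephone call".
- Section 8, all four categories: "the caller, either patient or witness, for an individual with a stroke event".
- Section 9, patients: the nurse "will ask patients if they were the person who made the call leading to hospital admission", and invites those who say that they were.
- Section 9, witnesses: "if they say that a witness made the call, then that witness will be approached".
- Section 11, which repeats the steps: "If the patient was not the person who made the call leading to hospital access they will be asked who did".

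Two other places are wider. Section 1 describes witnesses by their having made the first contact with medical services and does not mention a telephone. Section 9 also lets the research nurses approach accompanying carers and relatives directly, so that severe strokes are covered.

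**The concern.** Someone who walks into A&E, or is driven there, need not have rung any service. The matrix names this route as one to be sampled, yet the question that decides who is invited presupposes that somebody called.

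The group matters to the study question. Section 1 frames access as the decision whether to call emergency services at once, and Section 3 asks how and why people did or did not seek immediate help. People who went straight to A&E without calling sought emergency care but did not use the telephone, which is a different response both from dialling 999 and from ringing a GP. An awareness intervention would want to know why they did so. Section 8 undertakes to cover the range of experience within each part of the matrix, and Section 13 rests validity on purposive sampling, saturation and attention to negative cases. If screening passes over this group, the column could fill with callers and still carry a label that includes direct arrivals, and the tally of completed interviews would not show it.

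**Working it through.** **The plan's own count.** Four cells of 12 give 4 × 12 = 48, which agrees with 24 patients + 24 witnesses = 48. The column that includes direct A&E arrival holds 12 + 12 = 24 places, half of the total. The protocol does not divide these 24 between 999 callers and direct arrivals, so the intended number of direct arrivals could be anything from 0 to 24.

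**Tracing the screening steps.** No further arithmetic applies. The check is to take each kind of event in that column through Sections 8, 9 and 11 as written.

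| Event | Did the patient make the call? | Next step as written | Result |
| --- | --- | --- | --- |
| Patient dials 999 | Yes | Patient invited | Enters |
| Witness dials 999 | No | Witness identified and approached | Enters |
| Patient or companion first rings a service, then goes to A&E | Yes, or a companion did | As above | Can enter |
| Patient goes to A&E, nobody rings | No | Asked who called; there is no answer | No route |
| Companion takes patient to A&E, nobody rings | No | Asked who called; there is no answer | Only the direct approach to accompanying carers and relatives |

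The steps have two branches, that the patient called or that someone else did. There is none for the case where nobody called.

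**Whether other text closes the gap.**

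- *Direct approach to carers and relatives (Section 9).* It could reach the companion in the last row. Its stated purpose is severe strokes, it does nothing for patients who brought themselves in, and a companion reached this way still fails the telephone wording of Section 8.
- *Section 1's wider description.* It covers the companion in substance, but it concerns witnesses only and is not carried into the rules that Sections 8, 9 and 11 apply.
- *Section 9's statement that all acute stroke patients are eligible.* It is tied to treatment received and does not waive the caller condition.
- *Section 8's provision to keep sampling until nothing new emerges.* Further participants would pass through the same question.

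**Timing.** Patients are approached 1–2 days after stroke and interviewed at 7 ± 2 days, that is days 5 to 9. Someone passed over at screening is unlikely to be recovered once that window has closed.

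**The case against.** The strongest reply is that *call* is used loosely. The word *telephone* appears only in the witness definition, and the screening question does not contain it. Section 8 itself lists direct A&E arrival among the routes of its callers, which suggests that the authors meant whoever initiated contact. The nurses are to be briefed on the study. Section 10 expects to exclude witnesses only by reference to the sampling matrix, apart from its age, capacity and communication criteria, and the matrix names direct A&E. If *call* is read as Section 1's first contact, the rules can be followed together.

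Much of this stands as evidence of intent: nothing suggests that the authors wished to leave these people out, and no exclusion criterion does so. It does not settle how the question will be asked and answered. A patient who took themselves to A&E and is asked whether they made the call may truthfully say no, and recruitment across the stroke units should not depend on each nurse's reading of the word. The softer passages also concern witnesses, not patients who came in alone.

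A reader might go further and infer that nobody who went direct to A&E can be recruited, or that the column must consist of 999 callers only. The protocol does not support either. Direct arrivals who first rang a service can pass the question, and some companions can be reached through the direct approach.

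**Conclusion.** The point holds as a mismatch between the matrix and the entry rules. On the literal wording, a patient who reached A&E without anyone calling has no route into the study, and a companion who took them there has only a partial one. This rests on reading *call* as a call to a service, which its pairing with 999, GP and NHS Direct and the term *caller* favour but do not prove.

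The effect is on the range of access behaviour covered. The documents give no share for arrivals without a call, so its size cannot be stated. It is tempting to assume a share and count lost interviews: at 5% to 20% of the column (an assumption without support in the protocol), 0.05 × 24 = 1.2 and 0.20 × 24 = 4.8, or about 1 to 5. Those would not be lost interviews. The cells still fill to 12, other participants take the places, and the matrix sets no quota for direct arrivals. The total of 48 and the method of analysis are untouched.

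This is a wording correction that should be made, ideally before recruitment starts. It is not a defect that undermines the study.

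**What to change.** In Sections 8, 9 and 11, replace the references to having made the call, or the initial telephone call, with one definition in line with Section 1: the participant is the person, patient or witness, who made the initial contact with medical services, by telephone or by going to A&E or taking the patient there. Reword the nurse's screening question and its follow-up to match, so that the case where nobody telephoned has an answer. Record the mode of access for each event (999, direct to A&E with or without a prior call, GP, NHS Direct, other), so that the make-up of the 24-place column can be reported.

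The cost is revised text in three sections and in the nurse briefing. No interviews are added and the matrix is unchanged.
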